#### Control Arm

In the control group, participants will attend the standard 15-week Transform Program, with education sessions delivered through standard participatory adult learning sessions by health educators from ICM on the topics of income creation, education, food security, health, and resilience, with key messages consistent with the soap opera videos. No specific educational information will be provided regarding measles and polio vaccination, and no specific reminders regarding measles and polio vaccinations will be provided.

### Outcomes

The primary outcome will be the coverage of the first dose of any MCV among the participants’ children aged 1 year. This will be measured at 6 months after completing the Transform Program. Eligible children must be legal dependents of Transform Program participants and reside in the same household. MCV coverage will be calculated as the proportion of children who have completed at least 1 dose of MCV among the total number of eligible children.

Secondary outcomes will include (1) the first-dose MCV coverage at the family level, which will be determined by the number of participants whose eligible children have completed at least 1 dose of MCV by age 1 year (a family will not be considered covered if any eligible child does not receive the vaccine); (2) coverage of 2-dose MCV among children aged 2 to 6 years; (3) the rate of 2-dose MCV coverage at the family level; (4) polio vaccination coverage, calculated as the proportion of children aged 1 year who will have received at least 3 doses of polio vaccines (IPV or OPV); (5) the polio vaccination coverage at the family level; and (6) participants’ mean knowledge and attitudes score toward measles and polio vaccines, which will be measured by a 10-item questionnaire administered at the beginning and end of the Transform Program. Outcomes 1 to 5 will be assessed 6 months after the completion of the Transform Program. We will conduct subgroup analyses by children’s sex and by province. In addition, we will conduct a process evaluation to assess its relevance, applicability, and feasibility using qualitative research methods.

### Sample Size

The first-dose MCV coverage in the control arm is estimated to be 80% in 2023 based on the WHO report [27]. We estimate that the rate will increase by at least 10% after the intervention. To detect this difference with 90% power using 2-sided testing at the 5% signiﬁcant level, assuming a mean cluster size of 5 children aged 1 year per cluster and an intracluster correlation coefficient of 0.12, we estimate that at least 156 clusters (communities; 78 per arm) will be needed to detect the proposed effect size. To maximize the statistical power, we will recruit all 180 clusters participating in the Soap Opera Trial. We assume that 900 children aged 1 year (450 per arm) will be evaluated for the primary outcome. Because there are 30 participants (ie, parents or grandparents) in each community, we will include them all for a total of 5400 participants in the trial activities.

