**Results:**

Between January 31 and February 29, 2024, we recruited 66.9% (3613/5400) of the participants for the trial. Data collection is ongoing at the time of manuscript submission.

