Despite the DOH’s continuing efforts to improve vaccination coverage through mass immunization campaigns and annual public health initiatives aimed at increasing awareness, challenges persist in fully reaching the WHO targets, especially in the most remote and underserved communities, often referred to as the “last mile” [11-13]. Specifically, vulnerable populations residing in hard-to-reach communities pose a significant challenge for the delivery of vaccination campaigns and services. These populations are also often those living in poverty or of low socioeconomic status [11]. Although data specifically from the Philippines are sparse, studies from various low- and middle-income countries consistently report lower vaccination rates among households with lower socioeconomic status [14-17]. This inequality in vaccination is often observed in rural areas or urban slums, where public health campaigns and interventions are difficult to implement [14]. Another challenge to vaccination programs is vaccine hesitancy, which largely stems from concerns about vaccine safety, importance, and effectiveness. In the Philippines, vaccine hesitancy has been exacerbated by the controversy surrounding the Dengvaxia scandal in 2016, which involved a dengue vaccine that was prematurely introduced by the Government of the Philippines and the WHO and was associated with several deaths among vaccinated children, fueling skepticism and fear among the public regarding the safety and efficacy of vaccines in general [18]. Moreover, the unprecedented disruption caused by the COVID-19 pandemic has temporarily halted routine immunization schedules, further complicating the delivery of essential vaccination services [19,20]. The pandemic’s impact on health care systems has diverted resources and attention, causing delays in routine vaccinations against diseases such as measles and polio, and reversing gains made in previous years [19,20].

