### Eligibility and Recruitment

Participants are eligible to be included in our trial if they (1) reside in the participating communities where ICM recruits for the Transform Program, (2) meet the criteria and definition of living in extreme poverty based on ICM’s screening, and (3) give informed consent to participate in the health-education sessions, which include the delivery of our toolkit. Those who refuse to participate will not be included in the trial. Participants will be recruited and screened with an ICM poverty scorecard that uses asset-based scoring loosely based on the Progress out of Poverty Index developed for the Philippines and self-reported household income [25]. The items used for computing the score are elicited through in-person enumeration and home visits. Participants in households that meet the definition of living in extreme poverty by income (<22 PHP [US $0.38] per person per day) are prioritized for recruitment into the Transform Program. There are 30 eligible participants in each community to start the ICM Transform Program. In previous programs, 27% of transform participants went to bed hungry at least once per week. All participants are women with specific parental education levels and have an illiteracy rate of 15%. On average, there are 3.3 children per participant’s immediate family, and 1 child per family falls within the vaccination age for measles and polio, which is between 12 months and 6 years. Children in the household are often malnourished. Economic deprivation is a common unifying factor across households.

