## Results

This study was funded in 2021 and registered at ClinicalTrials.gov (NCT06218368) on January 23, 2024. Participant recruitment was launched on January 31, 2024, and completed on February 29, 2024. A total of 3613 participants have been recruited for the trial. Data collection is ongoing and is expected to be completed by June 30, 2025, and we plan to disseminate the results by September 30, 2025. We will disseminate the trial results through research articles and policy briefs. We aim to publish our results in leading international medical journals and present them at national and international conferences. The total lifespan of the study will be 23 months, as shown in Table 2.

**Table 2 table2:** Study timeline.

			Study period (months)										
			1-3		4		5-8		9-10		11-20		21-23

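### Recruitment closed at 3613 of 5400 participants, but the sample-size section still states 900 one-year-olds and 90% power; on the planned ratio about 600 children and 81–87% power are expected.

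*Protocol article*

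**What the plan says.** The Sample Size section sets the planning values. On the control arm: "The first-dose MCV coverage in the control arm is estimated to be 80% in 2023 based on the WHO report". On the effect: "We estimate that the rate will increase by at least 10% after the intervention". With 90% power, a two-sided 5% test, 5 one-year-olds per community and an intracluster correlation of 0.12, it asks for at least 156 communities (78 per arm). It then takes all 180 communities of the Soap Opera Trial, with 30 participants each (5400 in total), and states: "We assume that 900 children aged 1 year (450 per arm) will be evaluated for the primary outcome".

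The Results section gives January 31 to February 29, 2024 as the recruitment period, describes recruitment as completed, and says: "A total of 3613 participants have been recruited for the trial". The abstract puts it as "we recruited 66.9% (3613/5400) of the participants for the trial". Only data collection is described as ongoing.

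The Strengths and Limitations section does not mention the shortfall. The article does not say how many communities were enrolled or how many one-year-olds were found.

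**The concern.** The article carries two sample sizes: a target of 5400 participants and 900 children, and a closed recruitment of 3613. Its power statement belongs to the target. A reader who takes the Sample Size section at face value will expect 450 children per arm behind the primary comparison and will judge a null result against at least 90% power. With a third fewer participants, neither expectation is safe. The reader cannot correct it either, because the communities and one-year-olds enrolled per arm are not given.

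**Working it through.** **Inputs.** From Sample Size: 80% versus 90%, two-sided 5%, 90% power, m = 5 children per community, ICC = 0.12, 180 communities, 30 participants each. From Results: 3613 participants, recruitment completed. From Randomization and Blinding: 1:1 allocation.

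**1. Reproduce the plan.** Unpooled two-proportion formula: n = (1.96 + 1.2816)² × (0.80×0.20 + 0.90×0.10) / 0.10² = 262.7 per arm. Design effect: 1 + (5 − 1)×0.12 = 1.48. Then 262.7 × 1.48 = 388.8 children per arm, and 388.8 / 5 = 77.8, so 78 communities per arm and 156 in total. This matches the article and shows that the 10% increase means 10 percentage points.

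**2. Power of the full target.** 90 communities × 5 = 450 per arm. Effective n = 450 / 1.48 = 304. SE = √(0.25/304) = 0.0287. Power = Φ(0.10/0.0287 − 1.96) = 93.7%.

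**3. Expected children after recruitment.** The plan has 5 one-year-olds per 30 participants, or one per 6. This is an inference; the article does not state it as a ratio. 3613 / 6 = 602 children, about 301 per arm.

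**4. Power at 602 children.** The number of communities is not reported, so the two ends are shown.

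| Case | Children per community | Design effect | Effective n per arm | Power | Detectable difference at 90% power |
|---|---|---|---|---|---|
| 180 communities, equal sizes | 602/180 = 3.35 | 1 + 2.345×0.12 = 1.281 | 301/1.281 = 235 | 86.6% | 10.5 points |
| 180 communities, Poisson sizes (CV² = 1/m) | 3.35 | 1 + 3.345×0.12 = 1.401 | 301/1.401 = 215 | 83.4% | 10.9 points |
| About 120 communities (3613/30) | 5 | 1.48 | 301/1.48 = 203 | 81.4% | 11.2 points |

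A pooled-variance formula gives 86.1% and 80.9% for the first and last rows, so the choice of formula matters little. The detectable difference solves d = 3.2416 × √[(0.16 + (0.8 + d)(0.2 − d)) / effective n].

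**5. What would restore 90% with 180 communities.** Solve 90m / (0.88 + 0.12m) = 262.7: m = 231.2 / 58.5 = 3.95, or about 712 children (356 per arm). The pooled formula gives about 725 (363 per arm). Against 3613 participants, either is about one child per 5 participants instead of one per 6.

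**The case against.** The strongest defence is that nothing here is miscalculated. The Sample Size section is an a priori calculation in planning language, it reproduces exactly, and a protocol ordinarily keeps its design target. The abstract also prints 3613 over 5400 openly. All of that stands. What remains is that recruitment is described as finished, the evaluable number and the power are left unqualified, and no sentence links the two.

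Second, the count of 602 is inferred. The Eligibility and Recruitment section says that "1 child per family falls within the vaccination age for measles and polio, which is between 12 months and 6 years". Read as stopping at the sixth birthday, that spans five age-years, giving 3613/5 = 723 children and about 90% power with 180 communities. Read as including age 6, as the secondary outcome for ages 2 to 6 years suggests, it spans six age-years and gives 30/6 = 5 per community, which is the plan's own figure. The second reading fits better, but a reader should not conclude that 90% power has certainly been lost.

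Third, other unstated quantities could move power either way. An ICC near 0.05 with 180 communities, or a variance reduction of about 11% from the planned covariate adjustment (1 − 235/262.7), would bring it back to about 90%. Both are assumptions without support in the article. In the other direction, the calculation allows nothing for missing child records, which the limitations expect.

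Two stronger readings are tempting and do not hold:

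- A reader might say that 301 per arm misses a minimum of 78 × 5 = 390. That benchmark applies only at 5 children per community. With 180 smaller clusters, about 356 to 363 per arm suffice.
- A reader might note that the Background says studies from low- and middle-income countries "consistently report lower vaccination rates among households with lower socioeconomic status", assume 70% control coverage, and report power of 65–71%. The article gives no 70% figure for measles. Its lowest first-dose figure is 75% (national, 2018), and its figure of around 70% is for polio. It also says Philippine data on this are sparse.

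**Conclusion.** The concern holds as a matter of unrevised figures. The article states 900 evaluable children and 90% power beside a completed recruitment of 67% of target. On the planned ratio of one-year-olds to participants, at 80% versus 90% and ICC 0.12, about 602 children are expected. The chance of missing a true 10-point effect rises from about 6% at the full target to about 13% (all 180 communities, equal sizes) or 19% (about 120 communities).

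This is a moderate loss and does not make the trial unviable. The result rests on two things the article does not report: the number of one-year-olds enrolled and the number of communities they come from.

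**What to change.** Keep the calculation in Sample Size, and label 5400 participants, 900 children (450 per arm) and 90% power as the original targets. Beside them, state the communities, participants and baseline one-year-olds actually enrolled in each arm, with the mean cluster size. Restate the power for 80% versus 90%, or the difference detectable with 90% power, for that sample. Baseline coverage pooled over the arms, from the February 2024 survey, can serve as a sensitivity value for the 80% assumption. It should not replace it, because baseline coverage is not control-arm coverage 6 months after the program. Add the shortfall to the limitations.

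The cost is a recalculation and a few sentences, with a slightly less favourable stated power. No outcome, analysis rule or enrolment changes.

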### Data Collection

To collect primary and secondary outcome data, we will review the individual immunization records of children issued by the DOH for both the baseline and endline periods. To supplement the data retrieved from immunization records, we will also conduct pre- and postintervention surveys using structured, closed-ended questions to collect data on study participants’ sociodemographic information, self-reported vaccination status of their children, and their knowledge and attitudes toward measles and polio vaccines.

To assess the self-reported knowledge and attitudes toward measles and polio vaccination, we will distribute a survey to all participants before and after the intervention. In this survey, 2 items with 5-point Likert-scale responses will be used to assess vaccination attitudes, yielding a total score ranging from 1 to 10. The two items are (1) How much do you agree with the statement “Measles and polio vaccines are safe and effective”? and (2) How much do you agree with the statement “My concerns about vaccine-related side effects deter me from getting my children vaccinated”? All the Transform Program participants in both arms will participate in the pre- and postprogram survey. The ICM team will conduct primary data collection as part of their trial operations, and all personally identifiable information will be removed before sharing it with the study investigators. The survey questions will be administered by ICM staff through in-person interviews. In addition, to enhance the accuracy of the data collected, survey administrators from ICM will verify the vaccination status of the participants’ children by inspecting their vaccination cards. All participants of the Transform Program will be asked to complete the survey before and after the Transform Program as part of the ICM’s standard evaluation process. Preintervention surveys will be completed in February 2024, and postintervention surveys will be completed in August 2024. Vaccination data collection will be validated with local government vaccination records by June 30, 2025.

The ICM surveys will be conducted using SurveyCTO, which stores uploaded data on Amazon Web Services servers. All data will then be backed up using Boxcryptor, which encrypts cloud-based files. Personal identifiable data will be shared only after encryption and will be password-protected. Survey participants will provide consent through the ICM’s survey and data collection processes. The ICM’s survey team will conduct primary data collection as part of their program operations, and all personally identifiable information will be removed before being shared with the investigators of this study. The data will only be analyzed at the group and subgroup levels, and individuals will never be isolated during the process.

### Statistical Analysis

The data will be analyzed following an intent-to-treat approach and at the individual level. Sociodemographic characteristics of community members will be summarized descriptively using means (or medians) or proportions. For the primary and secondary proportion-based outcomes, the absolute differences in vaccination coverage between the intervention and control arms 6 months after the end of the Transform Program will be estimated using the generalized estimating equation models with a logit link while adjusting for baseline vaccination levels and covariates, including sex, age, and province. The odds ratio and 95% CI will be calculated to express the treatment effect. Preintervention and postintervention survey scores in knowledge and attitudes toward measles and polio vaccines will be calculated for the 2 arms, respectively. Generalized estimating equation models will be used to assess the effect of the toolkit on the postintervention knowledge and attitude scores, while adjusting for baseline level and covariates. Subgroup analyses by the 4 bases will be performed. Analyses will be conducted using either Stata (StataCorp) or R software (R Foundation for Statistical Computing). A 2-sided *P*<.05 will be considered statistically significant for the primary outcome analysis. For other analyses, *P* values will be computed and interpreted as the level of statistical evidence against prespecified null hypotheses.

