**Methods:**

Developed with local stakeholders, our intervention consists of a 10-minute video and vaccination reminders delivered by health trainers. It is embedded within the Soap Opera Trial, a large cluster randomized controlled trial conducted by the International Care Ministries that evaluates a 15-episode soap opera series combining drama with aspirational messages on hope, self-worth, and education, aimed at improving participants’ knowledge and practices in health, hygiene, nutrition, and livelihood. A total of 180 communities with 5400 participants will be randomly assigned to the intervention and control arms. By leveraging an existing community-based education program on health and livelihood run by our local partner, the proposed intervention will be delivered to participants in the intervention arm of the existing program, while those in the control arm will receive standard participatory adult learning sessions on health education. The primary outcome is the first-dose measles-containing vaccine coverage among participants’ children aged 1 year. Secondary outcomes include the 2-dose measles-containing vaccine coverage among children aged 2 to 6 years, polio vaccination coverage among children aged 1 year, and participants’ knowledge of measles and polio vaccines. The absolute differences in these outcomes between the intervention and control arms will be estimated using generalized estimating equations while adjusting for baseline levels and covariates. In addition, we will conduct a process evaluation.

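### The protocol promises an absolute difference in coverage and is sized on one, but names the odds ratio from a logit-link GEE as the effect measure with a CI

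*Protocol article*

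**What the plan says.** The Methods paragraph of the Abstract names one kind of effect: "The absolute differences in these outcomes between the intervention and control arms will be estimated using generalized estimating equations". It does not mention an odds ratio.

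The Statistical Analysis section opens the same way for the primary outcome and the proportion-based secondary outcomes: "the absolute differences in vaccination coverage between the intervention and control arms 6 months after the end of the Transform Program will be estimated". The same sentence fixes the model: these differences "will be estimated using the generalized estimating equation models with a logit link", adjusted for baseline vaccination levels, sex, age and province. The next sentence reads: "The odds ratio and 95% CI will be calculated to express the treatment effect". The section gives no CI for the absolute difference and does not say which of the two measures is primary.

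The Sample Size section sets the design values: "The first-dose MCV coverage in the control arm is estimated to be 80% in 2023" and "We estimate that the rate will increase by at least 10% after the intervention".

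**The concern.** A logit-link GEE has a log odds ratio as its treatment coefficient. Turning that fit into a difference in coverage takes a further step. The article names the difference as the thing to be estimated, then assigns the reporting of the effect, with its CI, to the odds ratio.

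What is at stake is the headline result. The design question is how many percentage points coverage rises. First-dose coverage is a common outcome (80% or more expected in both arms), and there the odds ratio lies far from the risk ratio and does not correspond to a fixed number of points. With the two measures unranked, the choice of which to lead with stays open until the data are in.

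**Working it through.** **Inputs, all from the Sample Size section:** control coverage 80%; a rise of 10%; 90% power; two-sided 5%; 5 children per cluster; ICC 0.12; 156 clusters needed (78 per arm); 180 planned.

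**1. Reproduce the stated number, to see which scale it is on.**

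- Design effect: 1 + (5 − 1) × 0.12 = 1.48.
- Risk difference, unpooled variance: n = (1.960 + 1.2816)² × (0.8×0.2 + 0.9×0.1) / 0.10² = 262.7 children per arm. Then 262.7 × 1.48 / 5 = 77.75, so 78 clusters per arm and 156 in total. This is an exact match.
- Pooled variance: 266 × 1.48 / 5 = 78.7, so 79 per arm (158 in total), close to the stated figure.
- 10% read as relative (80% to 88%): 436.1 × 1.48 / 5 = 129.1, so 130 per arm. No match.
- Log odds ratio scale: (1.960 + 1.2816)² × (1/0.16 + 1/0.09) / (ln 2.25)² = 277.4. Then 277.4 × 1.48 / 5 = 82.1, so 83 per arm (166 in total). No match.

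The trial is sized on a 10-point absolute difference.

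**2. The same effect on three scales at the design values.**

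- Difference: 0.90 − 0.80 = 0.10
- Risk ratio: 0.90 / 0.80 = 1.125
- Odds ratio: (0.9/0.1) / (0.8/0.2) = 2.25

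**3. The odds ratio does not fix the number of points.** The control rates other than 80% are assumptions, used to show the range.

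| Control coverage | Points implied by OR 2.25 | OR implied by +10 points |
|---|---|---|
| 70% | +14.0 | 1.71 |
| 75% | +12.1 | 1.89 |
| 80% | +10.0 | 2.25 |
| 85% | +7.7 | 3.35 |

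**4. Can the specified model deliver the difference?** In 200 simulated trials (180 clusters of 5, ICC 0.12, 80% versus 90%), a logit-link GEE with terms for arm and sex was fitted. Coverage was then predicted with every child set to each arm in turn, and the two predictions were averaged and subtracted. The mean difference was 0.098 (SD across trials 0.029), and the odds ratio from the mean coefficient was 2.23. The model yields the promised quantity once this step is added.

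**5. Does the scale change the power?** The effective number per arm is (clusters / 2) × 5 / 1.48.

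| Clusters | Effective n per arm | Power, difference scale | Power, log odds ratio scale |
|---|---|---|---|
| 156 | 263.5 | 90.1% | 88.5% |
| 180 | 304.1 | 93.7% | 92.4% |

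**6. Effect of adjusting for baseline status.** The document gives no baseline coverage, so this step rests on assumptions. Suppose baseline status is entered per child, vaccinated children stay vaccinated, and a share b is vaccinated at baseline in both arms. Among children unvaccinated at baseline, the odds at follow-up are (0.8 − b)/0.2 in the control arm and (0.9 − b)/0.1 in the intervention arm. The adjusted odds ratio is then 2(0.9 − b)/(0.8 − b): 2.33 at b = 0.2, 2.5 at 0.4, 3.0 at 0.6 and 4.0 at 0.7. The overall difference is 10 points in every case.

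**The case against.** The strongest reply is that the text can be read as promising both measures, an absolute difference in one sentence and an odds ratio in the next. A logit-link GEE followed by standardisation is an ordinary way to get a difference, and an article may leave the post-estimation command and the type of CI to an analysis plan that is not shown. This stands in part. The missing command alone would not be a finding. What remains is what the article itself states: a difference is promised, and a different quantity is then named as the expression of the treatment effect, with the only CI. An analysis plan could add the step, but the two statements in the article would still need to be reconciled.

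A reader might infer more than the document supports:

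- **That the difference will never be estimated.** The Abstract and the Statistical Analysis section both say that it will be, and step 4 shows that the specified model can supply it.
- **That the result could not be compared with the design effect.** The Outcomes section defines coverage as a proportion of eligible children, so arm percentages will exist, and 2.25 is the odds ratio counterpart of the design values.
- **That the adjusted odds ratio would be 3 or 4.** That needs 60% to 70% of these children to be vaccinated at baseline, which the document does not state. The first dose is due at 9 months, and follow-up comes about 9.5 months after the start (15 weeks plus 6 months). If age 1 year means age at follow-up, many children were too young for the dose at baseline and the shift would be smaller. The text also does not say whether baseline levels are taken per child or per community.

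**Conclusion.** The point holds as an inconsistency in the primary effect measure. The article promises, and is sized on, an absolute difference in coverage, but it names the odds ratio as the measure of effect. At the design values this is 2.25 against 10 percentage points and a risk ratio of 1.125. Adjustment for baseline status can move the odds ratio further from 2.25, by an amount that depends on unstated baseline coverage.

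It does not follow that the sample size is wrong or the test invalid. The 156 clusters are already on the difference scale, and the 180 planned give over 92% power on either scale under the protocol's own assumptions. A null difference and an odds ratio of 1 are the same hypothesis. The logit link is acceptable as a working model. The consequence lies in what the headline estimate means and in its being settled before the data are seen.

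**What to change.** In the Statistical Analysis section:

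- Name the adjusted risk difference in percentage points as the primary effect measure.
- Say that it is obtained by marginal standardisation from the logit-link GEE already specified, with a 95% CI that respects clustering (delta method on the robust variance, or a cluster bootstrap).
- Report the odds ratio with its CI as secondary.
- Apply the same rule to all coverage outcomes, at child and family level.

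The Abstract would then agree without change. The cost is about one sentence and one post-estimation step in Stata or R. No extra data, change of model or new sample size is needed.
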